#### Randomization

Participants will be randomized to 1 of 3 study conditions modeling different regulatory scenarios using stratified block randomization. We will use a randomization ratio of 1:1:1 to assign *N* = 50 per condition. The study biostatistician will create the randomization list that will be stratified by smoking heaviness (≤ 10 or > 10 cigarettes per day) and race (Black vs. non-Black) to ensure equivalent representation across groups. To avoid randomized non-starters and potential bias due to differential early attrition from prior knowledge of group assignment, randomization will occur at the time of visit 0 when participants first receive tobacco products specific to their assigned condition, and neither the research assistant nor participant will know the assignment in advance.

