#### Sample size and power calculations

Power was calculated using PASS software based on effect size estimates from pilot data where we detected an average change of 2.2 cigarettes, Cohen’s d = 0.68 [19]. To be sufficiently powered to detect a similar or smaller effect in the proposed study, we need *N* = 40 per group to achieve 80% power at two-sided alpha level of 0.05. Therefore, we will recruit 50 individuals per group for a total of 150 to allow up to 20% attrition and still achieve the specified power and required sample size of 40 per group. Due to our retention efforts, we expect our attrition rate may be even lower, as attrition in the initial study was less than the estimated 20% (i.e., attrition was 13%). For Aim 1, we will have sufficient power to detect a medium-to-large effect size (Cohen’s d = 0.64, Cohen’s f = 0.32). This corresponds to the ability to detect a difference of at least 2 cigarettes per day (SD = 3) or at least a 13% difference in percent days smoke-free (SD = 20%), consistent with effect size estimates from our work and other studies [19, 33]. For Aim 2, data from our initial work indicated differences across racial groups with a large effect size estimate (Cohen’s d = 1.21) [19]. With the proposed sample size, we will have sufficient power to detect a similar or smaller effect in the range of medium-to-large effect sizes (Cohen’s d = 0.64, Cohen’s f = 0.32) with 80% power at two-sided alpha level of 0.05 for the interactions of interest.

#### Analysis plan aim 1

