**Examine the impact of prohibiting menthol flavor in cigarettes and e-cigarettes on smoking behavior**. We will use mixed model analyses to evaluate changes in smoking behavior from Phase I (usual menthol cigarettes) to Phase II (assigned regulatory scenarios). Outcomes were selected to inform the impact of these policies on public health including changes in cigarette use, addiction, and appeal/acceptability of the alternative product. The primary outcome will evaluate changes in the number of cigarettes smoked per day during the 8-week period and will examine differences by regulatory scenario. Regulatory scenario (i.e., no menthol restriction, menthol prohibited in cigarettes only, menthol prohibited in cigarettes and e-cigarettes) will be a between-subject factor and time (week 0, 2, 4, 6, 8) will be a within-subject factor. The best-fitting variance-covariance matrix will be selected based on Schwartz Bayesian Criterion (BIC). We hypothesize (1) greater reductions in cigarette use in the context of menthol flavor prohibited in cigarettes vs. no menthol cigarette restrictions and (2) the greatest reductions in cigarettes per day in the scenario where menthol is prohibited in cigarettes but where menthol e-cigarettes remain available to substitute for cigarettes. We will use focused contrasts to compare the average change in cigarette use between groups to evaluate the effect of prohibiting menthol flavor in cigarettes, e-cigarettes, or both products. We will also estimate the average change in each group by 95% confidence intervals. Secondary outcomes will compare percent days smoke-free between regulatory scenarios, as well as changes in nicotine dependence, motivation and confidence quitting smoking, and intentions to quit smoking between groups using the same approach. Exploratory outcomes will compare percent days of e-cigarette use during the 8-week period, rates of continued product use after products are no longer provided, and quit attempts during the follow-up period to evaluate differences by group. We will use 0.05 significance level for the primary analysis of each aim and Bonferroni-Holm correction for multiple secondary and exploratory analyses. Exploratory analyses of sex as a potential predictive and moderating factor will also be performed by including sex as an additional between-subject factor in the models. We do not have *a priori* hypotheses regarding sex effects in this study and will focus on providing sex-specific effect estimates to inform future studies.

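### The Aim 1 model as described makes no use of week 0 as a baseline and omits both randomisation strata, so the change contrast is valid but less precise than the data allow

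*Protocol article*

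**What the plan says.** **Randomisation.** The Randomization section says: "The study biostatistician will create the randomization list that will be stratified by smoking heaviness". The full list of strata is "stratified by smoking heaviness (≤ 10 or > 10 cigarettes per day) and race (Black vs. non-Black"). Allocation is equal across the three arms. It takes place at visit 0, when the condition-specific products are first handed out.

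**Outcome.** Under Primary outcome measure, the outcome is average cigarettes per day over the past week, taken at weeks 0, 2, 4, 6 and 8. Under Visit schedule, the week before visit 0 is Phase I, when every participant smokes the usual menthol brand. The week-0 value is therefore a pre-treatment measurement.

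**Model.** In Analysis plan aim 1, scenario "will be a between-subject factor and time (week 0, 2, 4, 6, 8) will be a within-subject factor", and focused contrasts compare average change between groups. The secondary outcomes follow the same approach. Sex is added in exploratory models. In Analysis plan aim 2, race is added to the models already described, with race-by-scenario-by-time and race-by-time interactions. No described analysis mentions smoking heaviness.

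**Sample size.** The plan needs 40 per group "to achieve 80% power at two-sided alpha level of 0.05" and can detect a "medium-to-large effect size (Cohen’s d = 0.64, Cohen’s f = 0.32"). It recruits 50 per group "to allow up to 20% attrition and still achieve the specified power and required sample size of 40 per group".

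**The concern.** Because week 0 precedes any difference between the arms, its expected mean is the same in all three by design. A model that estimates a separate week-0 mean for each arm ignores this. Its change contrast subtracts each arm's own noisy baseline in full, whereas adjustment subtracts only the part that predicts follow-up. The estimate stays unbiased, but its variance is larger than it need be whenever the within-person correlation is below 1.

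The strata raise a related point. Factors used to balance the allocation normally belong in the primary model. The protocol's own pilot reports a large race difference (d = 1.21) and, in the Background, greater reductions among Black participants. If race predicts change, leaving it out of Aim 1 leaves explainable variation in the residual.

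At stake is precision in a trial sized for about 80% power at its stated effect. The data needed to recover it are already being collected.

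**Working it through.** **Inputs from the documents:** two-sided alpha 0.05, d = 0.64, 40 completers per arm, 50 recruited, 20% attrition, four post-baseline visits. **Assumed, because not given:** within-person correlation r from 0.5 to 0.9, compound symmetry, complete data, a Gaussian model, and d = 0.64 scaled to the SD of change. The article does not say whether its SD of 3 refers to change or to level.

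**Step 1: the plan's own figure.** For a two-sample comparison by noncentral t, d = 0.64 needs 40 per group, and power at 40 is 80.7%. The inflation is 40 / (1 − 0.20) = 50. Both stated figures reproduce. The smallest d with 80% power at 40 per arm is 0.634.

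**Step 2: variance with and without baseline adjustment.** Take unit variance at each visit and the mean of the four follow-ups.

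- Change from week 0, free baseline means: (1 + 3r)/4 + 1 − 2r = 1.25(1 − r).
- Common week-0 mean, or baseline as covariate: (1 + 3r)/4 − r² = (1 − r)(1 + 4r)/4.
- Ratio: (1 + 4r)/5.

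Power after adjustment uses d = 0.64 / √ratio with 40 per arm.

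| r | change | adjusted | ratio | variance saved | power (from 80.7%) | equivalent completers per arm, 40/ratio | detectable d, 0.634 × √ratio |
|---|---|---|---|---|---|---|---|
| 0.5 | 0.625 | 0.375 | 0.60 | 40% | 95.4% | 67 | 0.49 |
| 0.7 | 0.375 | 0.285 | 0.76 | 24% | 90.0% | 53 | 0.55 |
| 0.8 | 0.250 | 0.210 | 0.84 | 16% | 87.0% | 48 | 0.58 |
| 0.9 | 0.125 | 0.115 | 0.92 | 8% | 83.8% | 43 | 0.61 |

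If a single follow-up such as week 8 is compared with week 0, the ratio is (1 + r)/2. That gives 0.85, 0.90 and 0.95 at r = 0.7, 0.8 and 0.9, with power 86.6%, 84.6% and 82.6%.

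**Step 3: the strata.** A stratum main effect shifts all visits equally and cancels from change, so with complete data it alters nothing. A stratum-by-time term multiplies the change variance by 1 − R², where R² is the share of variation in change that the stratum explains.

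- R² = 0.05 gives power 82.6%, and R² = 0.10 gives 84.6%.
- If the pilot d = 1.21 is a race difference in change, with equal halves, R² = 1.21² / (1.21² + 4) = 1.464 / 5.464 = 0.27, and power is 91.1%.

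A simulation at r = 0.7 with 40 per arm agrees. With no race difference in change, adding both strata leaves the standard error of the change contrast at 0.136. With a race difference of d = 1.21 (in within-race SDs of change), the standard error falls from 0.160 to 0.137 and power rises from 71% to 81%.

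**Step 4: heaviness after baseline adjustment.** Heaviness is a two-level cut of cigarettes per day, the quantity that week 0 measures on a continuous scale. With normal data, a linear relation and a median split of baseline, adding the split leaves the residual variance unchanged: 0.285 at r = 0.7 and 0.115 at r = 0.9.

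**The case against.** The strongest reply is that this is a condensed article whose analysis plan is not shown, and that covariate lists and baseline parameterisation are usually settled there. Part of this stands. The article does not write out the scenario-by-time term for Aim 1 and does not rule out a common week-0 mean. The free mean per arm is inferred from the factor structure, the change contrasts and the three-way interaction in Aim 2. For heaviness the omission is silence, which a fuller plan could fill. For race it is more than silence, because Aim 2 adds race as an extra factor to the Aim 1 models.

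A second reply is that power is not as tight as 80.7% suggests. The article's own translation is to "detect a difference of at least 2 cigarettes per day (SD = 3"), which is d = 0.67 and gives 83.8% power at 40 per arm. At the pilot's 13% attrition about 43 per arm would remain (50 × 0.87 = 43.5), giving about 83% to 84% at d = 0.64. The mixed model also uses partial data from dropouts. This stands and limits the urgency, but it does not remove the gain.

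A third reply is that the size rests on an unreported correlation and a Gaussian model, while the plan chooses the covariance by BIC and allows transformation or count models. This also stands: the percentages are illustrative, and at r = 0.9 the gain is small.

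A reader might go further and infer that omitting the strata makes the standard error wrong. The documents do not support that as a general statement. For a change contrast, omission matters only if the strata predict change, and the error then tends to be on the conservative side. Nor do the strata gains simply add to the baseline gain, since heaviness largely repeats what baseline already carries.

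**Conclusion.** The point holds as one of efficiency. The Aim 1 model as described contains scenario and time only, treats a pre-treatment value as one more outcome level, and on the natural reading compares unadjusted change. A common week-0 mean would reduce the contrast variance by 24% at r = 0.7, 16% at 0.8 and 8% at 0.9. Power at d = 0.64 with 40 per arm would move from about 81% to 90%, 87% and 84%. These figures assume compound symmetry, complete data, a Gaussian outcome and d scaled to the SD of change.

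Race-by-time could add to this if race predicts change. The pilot suggests it may, but the article does not say that d = 1.21 is a difference in change.

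It would be tempting to conclude that the planned estimate is biased by chance baseline imbalance or that the sample size is wrong. Neither follows. Under randomisation chance imbalance is a matter of variance, stratifying on heaviness already limits it, and the stated 40 and 50 per group reproduce.

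**What to change.** In the Aim 1 model, state the scenario-by-time structure and constrain the week-0 mean to be equal across arms, or use week-0 cigarettes per day as a covariate for the follow-up visits. Include race and smoking heaviness, each with its interaction with time, because main effects alone recover nothing for the change contrast. Apply the same form to the secondary outcomes that have a week-0 value, which Table 1 shows for the PROMIS dependence measures and for quitting motivation and confidence. If a count model is used, keep the same principle and say how baseline enters.

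The cost is wording in the analysis plan, settled before the data are analysed. No new data, visits or participants are needed. If the full analysis plan already specifies this, a sentence saying so closes the point.

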
#### Analysis plan aim 2

**Investigate whether outcomes differ by race to understand the impact of the menthol policies on Black individuals given high rates of menthol cigarette use in this population**. Consistent with our initial work, we aim to recruit equal numbers of participants who identify as Black vs. non-Black and will stratify randomization by race. This will allow us to evaluate the impact of the various regulatory scenarios separately by race and to understand the potential benefit specifically for Black individuals who smoke, who are disproportionately impacted by the harms of menthol cigarette use. We will examine whether changes in the outcomes differ by race by including race as an additional between-subject factor in the models above. We will test race*regulatory scenario*time interactions to evaluate moderator effects and race*time interactions to evaluate race as a predictor of outcome. Planned post-hoc analyses will evaluate pairwise differences in changes from Phase I to Phase II to compare the magnitude of the effect of the policy scenarios separately by race (e.g., the reduction in cigarette use for Black participants if menthol is prohibited in cigarettes only vs. both cigarettes and e-cigarettes vs. no policy change). If the findings suggest important differences in the magnitude of the effect between Black vs. non-Black individuals, this can also inform future research aimed at examining effects among specific subgroups by race/ethnicity.

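### Aim 2 asks whether the size of the Phase I to Phase II change differs by race, but its named tests compare five-visit trajectories, and no stated test compares average change between races

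*Protocol article*

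**What the plan says.** Analysis plan aim 1 sets up the mixed model: scenario is a between-subject factor and "time (week 0, 2, 4, 6, 8) will be a within-subject factor". For the scenario comparison it then names a summary of change: "We will use focused contrasts to compare the average change in cigarette use between groups".

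Analysis plan aim 2 extends that model: "We will examine whether changes in the outcomes differ by race by including race as an additional between-subject factor in the models above". The tests it names are these: "We will test race*regulatory scenario*time interactions to evaluate moderator effects and race*time interactions to evaluate race as a predictor of outcome". Its Phase I to Phase II comparisons come afterwards: "Planned post-hoc analyses will evaluate pairwise differences in changes from Phase I to Phase II to compare the magnitude of the effect". The sentence goes on to say that these are done separately by race, and its example compares the three scenarios among Black participants.

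On error control, Analysis plan aim 1 says: "We will use 0.05 significance level for the primary analysis of each aim". The section on sample size and power states 80% power for the Aim 2 interactions at d = 0.64 (f = 0.32).

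**The concern.** The quantity of interest in Aim 2 is a difference between races in how much smoking changes from Phase I to Phase II. The null hypothesis of a race by time interaction over five visits is different: it says that the race gap is the same at every visit. The three-way interaction tests the corresponding statement for the race-by-scenario pattern.

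Two consequences follow. A rejection need not mean that one race reduced smoking more on average, because it can arise from one race responding earlier and the other later. And a steady difference, which the Background makes the natural expectation (changes evident at 2 to 4 weeks, with 8 weeks chosen to see whether they last), is tested with 3 or 6 surplus degrees of freedom.

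The within-race contrasts do not fill the gap. A clear scenario effect in one race and an unclear one in the other is not evidence that the two effects differ.

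**Working it through.** **Inputs from the protocol article.** 150 enrolled and 20% attrition, so 120 completers; equal Black and non-Black recruitment, so 60 vs 60 and about 20 per race-by-scenario cell; two-sided alpha 0.05; d = 0.64 as the stated detectable effect; d = 1.21 as the pilot's race difference; visits at weeks 0, 2, 4, 6 and 8.

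**Assumptions.** The covariance is left to BIC, so compound symmetry and AR(1) are used to show the range. d is in SDs of average change (mean of weeks 2 to 8 minus week 0). A steady effect means no race gap at week 0 and a constant gap at weeks 2 to 8. Data are complete.

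**1. The plan's own figure.** Two groups of 40 at d = 0.64 give 80.7% power by the noncentral t. A two-group F test with f = 0.32 and N = 80 also gives 80.7%. The stated 80% therefore reproduces as a two-group, 1-df comparison.

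**2. Degrees of freedom.**
- Race by time: (2 − 1)(5 − 1) = 4. Race difference in average change: 1.
- Race by scenario by time: (2 − 1)(3 − 1)(5 − 1) = 8. Race by scenario on average change: (2 − 1)(3 − 1) = 2.

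**3. Noncentrality for a steady effect.** Under compound symmetry the full interaction and the average-change contrast have the same noncentrality, so only the degrees of freedom differ.
- Race: λ = d² / (1/60 + 1/60) = 30d².
- Three-way, race difference d in one arm and none in the other two: λ = (2/3)d² / (1/20 + 1/20) = 6.667d².

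**4. Power (chi-square approximation; F with 114 denominator df in brackets).**

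| Test and effect | λ | Average-change contrast | Named test |
|---|---|---|---|
| Race, d = 0.64 | 12.29 | 93.9% (93.5%) at 1 df | 81.3% (79.4%) at 4 df |
| Three-way, d = 0.64 in one arm | 2.73 | 29.6% (28.9%) at 2 df | 16.8% (15.9%) at 8 df |
| Three-way, d = 1.21 in one arm | 9.76 | 80.5% (79.4%) at 2 df | 57.5% (54.1%) at 8 df |

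For race by time at d = 1.21, both tests are close to 100%.

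**5. The ceiling on the loss.** Where the contrast has exactly 80% power, race by time has 59.5% (58.3% by F) and the three-way test has 56.8% (54.8% by F). Over all effect sizes the largest chi-square loss is 21.8 points for 1 vs 4 df and 24.1 points for 2 vs 8 df. For race by time this range is reached at about d = 0.52, below the effect size the protocol states.

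**6. Dependence on covariance.** With the simple average-change contrast fixed at 80% and AR(1) errors:

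| Visit-to-visit correlation | Race by time (4 df) | Three-way (8 df) |
|---|---|---|
| 0.3 | 63% | 60% |
| 0.5 | 69% | 66% |
| 0.7 | 76% | 74% |
| 0.8 | 80% | 79% |
| 0.9 | 84% | 83% |

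**7. Rejection on shape alone.** Give the two races exactly the same average change, and let the race gap run linearly from +a at week 2 to −a at week 8, with a in SDs at a visit and 60 vs 60 completers. Under compound symmetry with correlation 0.5, race by time rejects 80% of the time at a = 0.3 (78% by F) and over 99% at a = 0.5. Under AR(1) with correlation 0.5 the F figures are 52% and 95%. A 1-df test of average change would reject at its nominal 5%.

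**The case against.** The other side has four good points.

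- **Detail left to an analysis plan.** The article never uses the word omnibus or gives degrees of freedom, and the contrast that represents an interaction could be fixed in an SAP that is not shown. This has some force. But the point rests on what is stated: the interaction terms are named, time is given five levels, focused contrasts are named for Aim 1, and the Phase I to Phase II comparisons in Aim 2 are placed within race.
- **A legitimate test.** Interaction followed by planned contrasts is a standard sequence, and a race difference in durability would be a real finding. This stands. A reader might infer that the named tests are invalid or inflate type I error. They do not: a rejection on shape is a correct rejection of their own null. It just does not answer the magnitude question.
- **A constructed reversal.** Nothing in the documents suggests a gap that changes sign between weeks 2 and 8. This also stands. The example shows what the test can respond to, not what is likely, and the race-specific estimates would help a careful reader notice it.
- **Size of the loss.** A reader might infer a general loss of about 25 points, or that race by time falls short of its stated power. The documents do not support either. At d = 0.64 race by time keeps about 80% even under compound symmetry, and the protocol does not commit to that covariance.

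**Conclusion.** The mismatch holds: the named Aim 2 tests address whether trajectories differ by race, the stated question is the magnitude of the Phase I to Phase II change, and no stated test compares that change between races. This does not depend on the covariance.

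The power cost does. For a steady effect under compound symmetry with 20 completers per cell, it is about 13 points at d = 0.64 for both the race test and the three-way test (race difference in one arm). It is at most about 20 to 25 points where the average-change contrast has about 80% power, and nil under strong serial correlation (AR(1) of about 0.8 or more). If effects build steeply over the weeks, the full interaction can gain power, though it is then partly testing shape.

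It would be wrong to infer that a better-matched contrast delivers the stated 80% for the three-way interaction at d = 0.64. The 2-df contrast has about 30% there, because of the roughly 20 completers per race-by-scenario cell. That is a separate limitation.

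**What to change.** Within the planned mixed model, define average change as the mean of weeks 2 to 8 minus week 0, and make these the primary Aim 2 tests:

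- **Moderation:** race by scenario on average change (2 df), reporting the race difference in each pairwise scenario contrast (B vs A, C vs A, B vs C) with its 95% confidence interval.
- **Prediction:** the race difference in average change (1 df), with its 95% confidence interval.

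Keep the full race by scenario by time and race by time interactions as supportive tests of whether the time course differs by race.

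The cost is a change of wording and a few contrast statements, with no new data or participants. The downside is that the primary tests no longer respond to time-course differences that leave average change equal; the retained interactions cover those. The 80% power statement for the three-way interaction needs separate attention.
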